#### DCE and SW Task Construction

The DCE (15) is a quantitative method to assess PP by asking respondents to state their choice over sets of hypothetical alternatives defined by combinations of different levels of several characteristics, hence the attributes. In the present research, respondents will be presented 12 choice tasks, following ISPOR guidelines. Each choice task consists of selecting between two alternative options which describe a hypothetical treatment A and treatment B (see Table 3 for an example of choice task). In each treatment, the five established attributes are linked to one of the three possible levels.

**Table 3 T3:** Example of a DCE choice task created for the study.

	**Treatment A**	**Treatment B**
How the treatment is given to you	Intravenous infusion lasting 24 h	Intravenous infusion lasting 12 h
Chance of survival 5 years after starting this cancer treatment	10% (10 out of 100)	10% (10 out of 100)
Chance of long-lasting skin problems	40% (40 out of 100)	10% (10 out of 100)
Chance of being extremely tired	60% (60 out of 100)	10% (10 out of 100)
Severity of hair loss	Weakening/thinning	No hair loss

NGene 1.2.1 software (31) will be used to create a Bayesian D-efficient design. Prior information used to generate this design was based on the previous literature and best guesses for the pilot study, and outcomes of initial analysis (conditional logit) of pilot data for the main survey. Dominant alternatives where one alternative is clearly “better” than the other alternative were excluded from the design. For both the pilot and the final design, a total of 36 unique choice tasks were generated, which were divided over three blocks; each choice task was assigned to only one of the blocks (each patient answered only 12 choice tasks). Patients will be randomized to either one of the blocks. Interactions between 5-year survival and risk or extreme tiredness, 5-year survival and risk of skin problems, and 5-year survival and mode of administration were included in the design.

The SW (17) is a method in which respondents are asked to indicate which attribute, among a provided list, they want to improve (i.e., to “swing”) from the worst to the best level first. After making this choice, respondents are asked to indicate which is the second attribute they want to improve from worst to the best. This is repeated until all attributes are ranked. Afterward, a drag-and-drop method allows patients to further adjust their selection after the ranking is completed. The order in which the attributes will be presented in the description will be randomized. Table 4 provides an example of a scenario with attributes and attribute levels.

**Table 4 T4:** Example of the SW choice task—attribute ranking.

	Drag the most important improvement here
**Severity of hair loss**	
Total hair loss → no hair loss	
**Chance of being extremely tired**	
60% (60 out of 100) → 10% (10 out of 100)	
**Chance of survival 5 years after starting this cancer treatment**	
10% (10 out of 100) → 40% (40 out of 100)	
**Chance of long-lasting skin problems**	
40% (40 out of 100) → 10% (10 out of 100)	
**How the treatment is given to you**	
Intravenous infusion lasting 24 h → oral treatment (pill swallowing)	
	Drag the least important improvement here

Participants will then be asked to assign points to each attribute they have ranked in the previous step. The first attribute automatically receives 100 points; participants have to assign points to all the other attributes (i.e., “weighting”). See Table 5.

**Table 5 T5:** Example of the SW choice task—point allocation.

The improvement of the following characteristic was found to be the most important for you:
**Chance of survival 5 years after starting this cancer treatment**
For this reason, we assign it a score of 100 points.
Please assign a score to the second most important improvement by moving the cursor on the bar below, so that it reflects its importance vs. the first.The second improvement was:
**How the treatment is given to you**
**  **
We ask you to do the same with all the improvements shown below.Warning! We remind you that if the first improvement is 100 points worth and you have assigned for example 50 points to the second improvement, to the third improvement you will have to assign a score lower than 50 points and so on for the subsequent ones classified by you as less important. Remember that you can go back and edit your answers at any time.
**Chance of being extremely tired**
**  **
**Chance of long-lasting skin problems**
**  **
**Severity of hair loss**
**  **

#### Education Tool

An educational tool will provide study participants with information regarding the related attributes, levels, and survey technique. The tool leverages digital technology to educate patients on the attributes and attribute levels and instruct them in completing the choice tasks associated with the two types of preference elicitation methods (i.e., SW and DCE) included in the study. The content and format of the educational tool adhere to plain language principles, are written at an intermediate reading level, include visualizations to demonstrate key learning points, and enable patients to practice completing several choice tasks using a fictitious medication (a cold medicine) as an example. Three videos will be created *ad hoc* with colored graphical animations accompanied by a descriptive voiceover. One video explains to the participants the five attributes and their levels. A second video describes the functioning of the DCE and a third video illustrates the functioning of the SW.

#### Psychological Measures

Health literacy refers to patients' ability to read, understand, and use healthcare information appropriately and the ability to apply and manipulate numerical concepts (32, 33). This construct has been conceptualized in terms of subjective health literacy or objective evaluations. In the present research, health literacy will be measured with the Chew's Set of Brief Screening Questions (32) and the Newest Vital Sign (33). The Chew's Set of Brief Screening Questions is a self-reported, validated subjective measure of health literacy containing three items. The Newest Vital Sign is an objective and validated measure of health literacy in which patients are given an ice cream nutrition label containing health-related information and they have to answer six questions about this nutrition label.

A health locus of control is defined as a generalized expectation about whether one's health is controlled by one's own behavior or by external forces (34). An individual with a high internal locus of control believes that outcomes are a direct result of his or her own behavior. In contrast, an individual with a high external locus of control believes that outcomes are a result of either chance or powerful other people, such as physicians. The health locus of control will be measured with the Multidimensional Health Locus of Control Scale—Form C (34), an 18-item, general-purpose, condition-specific locus of control scale that can easily be adapted for use with any medical or health-related condition.

### Statistical Analyses

The clinical objective of this study is to assess patients' preferences for relevant treatment attributes related to LC treatment alternatives. To determine preferences of study participants, attribute (level) estimates and the conditional relative importance of attributes will be explored in the DCE using conditional logit models. For the final analyses, preferences for attributes of NSCLC treatment random parameters logit (RPL) modeling and latent class analysis (LCA) will be considered. Final decisions on the modeling procedure will be made once data collection has been completed and explored. This decision will be based on model fit and clinical interpretation. Different models might be used to answer the different research questions in this case study. Heterogeneity of preferences and the impact of participant characteristics among which psychological variables will be investigated *via* LCA or subgroup analyses using RPL.

For the SW, each attribute is first ranked by the participants, and then the relative importance is indicated through point allocation. The rank order will be turned into weights using a rank-to-weight method, rank order centroid method (35). Using this approach, the average weight per attribute over the entire group of respondents is then calculated and it becomes possible to statistically investigate whether weights differ between subgroups.

The MAR and MAB values for benefits and risks of interest will be determined based on DCE outcomes.

The methodological objective of this study is to evaluate the similarity of DCE and SW in assessing preferences for treatment alternatives in NSCLC. The results of the DCE and SW will be compared qualitatively and quantitatively to evaluate whether the results are different when applying two different methods. As a first step, validity checks, completion time (through log information), dropout, and response to feedback questions will be compared between the two methods. Second, the relative importance of the included attributes will be compared between the two methods.

PP heterogeneity and the influence of participants' clinical (i.e., disease stage and line of treatment), socio-demographic (i.e., age, gender, and educational level), and psychological characteristics (i.e., health literacy and health locus of control) will be investigated by applying appropriate statistical models including LCA and/or subgroup analyses.

Finally, the evaluation of patients' perceived usefulness of the educational tool will be assessed by conducting descriptive analysis on patients' rating of efficacy and usefulness, as well as correlational analyses assessing associations between this rating and patients' health literacy and numeracy, and clinical and sociodemographic variables.

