The multi-stakeholder discussions resulted in the deletion of four characteristics: the severity of infections, severity of infusion reactions, probability of cognitive limitations, and probability of renal failure. All those characteristics were deleted because according to the clinicians they are deemed as rare in NCSLC. The severity of the nausea was deleted because it can be treated and controlled by other existing drugs. Since attributes should be unambiguous, clear, tradable, and distinctly different from other included attributes (30), the chance to carry out activities of daily living was deleted from the list because (a) it is difficult to find a univocal definition for that feature, (b) it overlaps with the other included attributes (it is an overarching theme encompassing the other, more specific, attributes), and (c) it may be interpreted differently by different patients. The attribute of treatment modality (i.e., how the treatment is given to you) was added because it differs across different treatments that have been developed for NSCLC and knowing whether this attribute actually influences patients' decisions could be valuable information in HTA and regulatory decisions. The final list is composed of five attributes with three levels each (see Table 2). The same attributes and levels have been implemented in both DCE and SW to allow for their comparison.

**Table 2 T2:** Attributes, definitions, and levels.

**Attribute**	**Definition**	**Levels**
How the treatment is given to you	How the cancer treatment is given to you and the length of time each treatment takes.	This can either be: - Infusion (injection administered into your veins) that requires a hospital stay of 1 day (about 24 h) - Infusion (injection administered into your veins) that requires a hospital stay of half a day (about 12 h) - Oral treatment (by swallowing), and no hospital stay is required

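### Swing-weighting weights are built from rank order alone although points are collected to show strength of preference, so the size of SW importance, and its comparison in size with the DCE, partly reflects the rank order centroid formula

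*Protocol article*

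**What the plan says.** The attributes are common to both methods: "The final list is composed of five attributes with three levels each", and "The same attributes and levels have been implemented in both DCE and SW to allow for their comparison" (Attributes and Levels Development).

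In the SW task (DCE and SW Task Construction), patients first rank the five worst-to-best improvements and then score them: "The first attribute automatically receives 100 points; participants have to assign points to all the other attributes". The example screen in Table 5 tells patients that the scores must fall with rank. If the second improvement has 50 points, then "to the third improvement you will have to assign a score lower than 50 points and so on".

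Statistical Analyses describes the data as follows: "each attribute is first ranked by the participants, and then the relative importance is indicated through point allocation". The next sentence gives the weighting rule: "The rank order will be turned into weights using a rank-to-weight method, rank order centroid method". It then goes on: "Using this approach, the average weight per attribute over the entire group of respondents is then calculated", and the same weights are to be examined between subgroups. The section also plans a quantitative as well as a qualitative comparison of DCE and SW, whose second step sets the relative importance of the attributes under one method against the other. The Discussion names the similarity of the two methods as a main methodological endpoint.

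**The concern.** The section names the points as the carrier of relative importance and then builds the weights without them. A ranking records which improvement matters more. The points record how much more, and that is what this task adds to a plain ranking. The rank order centroid (ROC) method replaces the patient's own spacing with one fixed spacing.

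Two planned results are exposed. First, two subgroups that rank the attributes alike but differ in how strongly they favour the top one will show no difference in weights. Second, the comparison in size with the DCE sets an estimate that can follow strength of preference against one whose spacing is imposed. A reader could then take a product of the formula for a finding about the methods. The Discussion also asks whether the DCE gives better information than SW, and removing the strength information from SW beforehand weakens that question.

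**Working it through.** The article prints no SW weight or error figure, so there is nothing to reproduce. The check asks what the stated rule does to the data the task collects.

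**Inputs from the protocol article.** There are K = 5 attributes. The top attribute is fixed at 100 points, later attributes score lower, and weights come from ranks by ROC. The point patterns below are assumptions, because the article gives no data.

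**Step 1: ROC weights.** The formula is w_i = (1/K) × Σ_{j=i..K} 1/j.

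- Rank 1: (1 + 1/2 + 1/3 + 1/4 + 1/5)/5 = 2.2833/5 = 0.457
- Rank 2: 1.2833/5 = 0.257
- Rank 3: 0.7833/5 = 0.157
- Rank 4: 0.4500/5 = 0.090
- Rank 5: 0.2000/5 = 0.040

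Every respondent receives these five values in some order. A simulation of the centroid (200,000 draws) gave 0.456, 0.257, 0.157, 0.090 and 0.040. Rescaled so that the top is 100, the rule imposes points of about 100/56/34/20/9, a top-to-bottom ratio of 11.4.

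**Step 2: point-based weights.** The formula is w_i = points_i / Σ points. All four patterns have the same ranking.

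| Assumed points | Sum | Point-based top weight | ROC top weight | ROC minus points |
|---|---|---|---|---|
| 100/95/90/85/80 | 450 | 0.222 | 0.457 | +0.234 |
| 100/80/60/40/20 | 300 | 0.333 | 0.457 | +0.123 |
| 100/50/25/12/6 | 193 | 0.518 | 0.457 | −0.061 |
| 100/20/10/5/1 | 136 | 0.735 | 0.457 | −0.279 |

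Differences are taken before rounding. For a fixed ranking, the point-based top weight can lie anywhere from just above 0.20 to near 1.

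**Step 3: subgroup tests.** Suppose two subgroups have identical ranks, one giving 100/90/80/70/60 and the other 100/30/20/10/5. Their point-based top weights are 100/400 = 0.25 and 100/165 = 0.61. Their ROC weights are the same, so the ROC difference is exactly 0.

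**Step 4: comparison with the DCE.** A mean of values between 0.040 and 0.457 stays in that range. DCE importances expressed as shares summing to one have no such limits. If all patients gave 100/20/10/5/1 and the DCE share for the top attribute were also 0.735, ROC would report a gap of 0.279 where the points show none. If all gave 100/95/90/85/80 and the DCE share were 0.457, ROC would report agreement where the points differ from the DCE by 0.234.

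**Step 5: what still moves.** Let a share q rank survival first, with the rest spread evenly over ranks 2 to 5. The mean survival weight is q × 0.4567 + (1 − q) × (1 − 0.4567)/4. For q = 100%, 80%, 60%, 40% and 20% this gives 0.457, 0.393, 0.328, 0.264 and 0.200. Within the limits, group means do follow the observed ranks.

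**The case against.** The strongest reply is that the article never says the points are dropped. It applies the phrase relative importance to the points and uses it again for the comparison with the DCE, so the points might be meant to enter there, and an analysis plan not shown could say so. What stands is that non-use of the points is inferred from the only rule stated. But the article does not leave the SW weight open, as it does the DCE model. It names one rule and its uses, and no stated analysis brings in the points.

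A second reply concerns size. The patterns in the table are assumed, and the first and last are extreme. With 100/50/25/12/6 the top weight differs by only 0.061. The gaps have both signs and could partly cancel in a group mean, and an error shared by two subgroups largely cancels in their difference. This stands: the table gives individual-level gaps, not an estimate of bias in the study's averages, and those gaps should not be set against a detectable difference between group means.

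A reader might infer that SW importance is wholly fixed by the formula and that no valid comparison with the DCE is possible. The article does not support that. Which attribute receives which value depends on the patient's ranking, as Step 5 shows. The order of importance can still be compared, and so can completion time, dropout, validity checks and feedback.

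The Table 5 instruction that later scores must be lower, which leaves no room for ties, is a separate question about the survey instrument. It does not affect ROC weights, and the analysis change does not depend on it.

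**Conclusion.** The point holds for the size of SW importance and not for its order. The stated rule imposes each respondent's spacing of weights, confines group means to 0.040–0.457, hides from the subgroup tests any difference in strength that leaves ranks unchanged, and allows a gap or an agreement in size with the DCE to arise from the formula.

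The ROC values and their limits follow exactly from having five attributes. How far the results would be distorted cannot be known before the points are seen. The range of −0.279 to +0.234 in the top weight rests on the assumed patterns. The conclusion also assumes that the rule stated in the article is the one to be used and that DCE importances are scaled as shares. The maximum acceptable risk and minimum acceptable benefit results come from the DCE alone and are not affected. The rule should be changed before analysis, because similarity of the two methods is a main methodological endpoint.

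**What to change.** In Statistical Analyses, replace the weighting sentence with text to this effect: the main SW weight for each attribute is the respondent's points for it divided by that respondent's total points. This weight is used for the group averages, the subgroup tests and the comparison in size with the DCE. ROC weights are reported as a sensitivity analysis, and any ROC-based comparison with the DCE is limited to rank order.

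The cost is a short edit. The points are already collected, so there is no extra patient burden and no change to the survey.

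There are two small downsides. Point-based weights depend on how patients use the scale, which the ROC sensitivity analysis addresses. Respondents who rank but do not finish the points would have no point-based weight. Under Handling Missing Data the comparison with the DCE is already restricted to those who fully completed both methods, so the loss falls on the SW-only analyses, where the ROC analysis can still include these respondents.

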### Participants

The study aims to recruit 510 NSCLC patients from three cancer treatment centers (*N* = 170 per center) in Italy (*N* = 340) and Belgium (*N* = 170). Italian patients will be recruited at the European Institute of Oncology and the National Institute of Cancer in Milan. Belgian patients will be recruited at the Respiratory Oncology Department and the Department of Thoracic Surgery of the KU Leuven University Hospital in Leuven. Each cancer center treats approximately 500 NSCLC patients yearly. NSCLC patients in different stages (stages I–IV) will be recruited and divided into two groups (see Figure 1): 255 early stages (stages I and II) and 255 later stages (stages III and IV).

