### Sample Size Estimation

For SW, no specific sample size is required since the sample size does not depend on the magnitudes of the utility differences (22). Therefore, the sample sizes will be dictated by requirements for the DCE. To the best of our knowledge, there are no statistical tools able to estimate the sample size for a DCE. Therefore, we referred to the literature to estimate the sample size for the present research. Most published choice experiments have a sample size of between 100 to 300 respondents (23). However, according to Bekker-Grob et al. (24), the minimum sample size depends on several criteria, including the question format, the complexity of the choice task, the desired precision of the results, and the need to conduct subgroup analyses (25, 26). Given this, we have determined that, based on the sample size requirements for both methods and taking into account the number of research questions this study anticipates to answer, a sample size of 510 respondents (170 per site) is expected to provide enough information to identify preferences in each country and comparisons across countries and disease groups with acceptable precision.

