### Handling Missing Data

Respondents who choose not to answer certain demographic or treatment history questions will be noted in the summary statistics, and their responses will be included in the DCE; however, if data required to assign an individual to a subgroup are missing, that individual will be excluded from the subgroup analysis (pairwise deletion). Respondents who do not answer at least one DCE question and at least one SW question in the survey, or who always select the same alternative (either treatment A or treatment B) in all of the DCE questions (“flatliners”), will be analyzed separately as a part of the quality assessment evaluation. For comparing DCE to SW, we will include respondents who fully completed both methods, whereas for the separate analyses on the DCE or SW, we will include respondents that completed parts of the methods.

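### Age, health literacy and locus of control are graded, yet the named routes from them to preference lean on subgroup comparison; if the scores are cut in two, a quarter to a half of the information could be lost

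*Protocol article*

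**What the plan says.** **The question.** Study Objectives makes it a clinical endpoint to learn to what extent preferences vary with disease stage, line of treatment, age, gender, education, health literacy and health locus of control.

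**The measurements.** Psychological Measures describes a three-item subjective literacy screen, an objective literacy test with six questions, and, for locus of control, "an 18-item, general-purpose, condition-specific locus of control scale". Age is asked in the survey, and no age bands are given.

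**The analyses (Statistical Analyses section).**
- SW: after average weights are computed, "it becomes possible to statistically investigate whether weights differ between subgroups". This paragraph names no other heterogeneity method.
- DCE: heterogeneity and the impact of participant characteristics, psychological variables among them, "will be investigated *via* LCA or subgroup analyses using RPL".
- A closing paragraph lists age, literacy and locus of control by name. It calls for suitable models, with LCA and subgroup analyses given as what these include.
- The final choice of model is deferred until the data have been collected and explored.

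**Related text.** Handling Missing Data says that "if data required to assign an individual to a subgroup are missing, that individual will be excluded from the subgroup analysis (pairwise deletion" is the rule. A graded analysis of literacy is planned, but only for the rating of the educational tool: "correlational analyses assessing associations between this rating and patients' health literacy and numeracy".

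No section states a cut-point, a number of groups, or an analysis of these scores as continuous predictors of preference.

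**The concern.** A subgroup comparison needs groups. Gender and stage group come as groups; age and multi-item scores do not. Grouping a graded score has three effects:

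- It lowers the power to detect a real gradient.
- It makes the answer depend on where the cut falls. The grouping is not fixed in this document and the modelling choice follows data exploration, so the cut could follow the data.
- It treats patients just either side of the cut as different in kind, and all patients within a group as alike.

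The Introduction says there is no empirical evidence on how these psychological aspects affect the preferences of lung cancer patients. A null finding on literacy or locus of control would therefore carry weight, and it could not be told apart from a loss caused by the grouping. The Sample Size Estimation section gives no power for this endpoint; its statement on precision concerns countries and disease groups.

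**Working it through.** **1. The plan's own figure.** The section states that "a sample size of 510 respondents (170 per site) is expected to provide enough information to identify preferences in each country". The counts agree: 3 × 170 = 510; 340 + 170 = 510; and the stage groups ("255 early stages (stages I and II) and 255 later stages (stages III and IV") give 255 + 255 = 510. The section also says that "there are no statistical tools able to estimate the sample size for a DCE", and it states no alpha, power or effect size. There is no power figure to reproduce.

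**2. Assumptions (not in the documents).** Two-sided 5% test; linear gradient; score roughly normal, or alternatively a 0–6 total for the six-question test; groupings ranging from two groups (50/50 to 20/80) to five equal groups.

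**3. Information kept.** Grouping keeps the share E of the score's variance that lies between groups. For a normal score cut once at quantile q, with φ the normal density at that quantile, E = φ² / [q(1 − q)]:
- 50/50: 0.3989² / 0.25 = 0.637
- 30/70: 0.3477² / 0.21 = 0.576
- 20/80: 0.2800² / 0.16 = 0.490

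For a flat 0–6 score cut at 4, the groups are 0–3 (mean 1.5, share 4/7) and 4–6 (mean 5, share 3/7), around an overall mean of 3. Between-group variance is (4/7)(1.5²) + (3/7)(2²) = 9/7 + 12/7 = 3. Total variance is (49 − 1)/12 = 4. So E = 3/4 = 0.75.

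**4. Power after grouping.** Where the full-scale test has 80% power, power after grouping is Φ(√E × (1.96 + 0.84) − 1.96).

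| Grouping | E | Lost | 510 act as | Power |
|---|---|---|---|---|
| Median split, normal | 0.637 | 36% | 325 | 61% |
| 30/70, normal | 0.576 | 42% | 294 | 57% |
| 20/80, normal | 0.490 | 51% | 250 | 50% |
| Flat 0–6, cut in two | 0.750 | 25% | 382.5 | 68% |
| Tertiles, trend | 0.793 | 21% | 405 | 70% |
| Quartiles, trend | 0.861 | 14% | 439 | 74% |
| Quintiles, trend | 0.897 | 10% | 457 | 76% |

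Worked line for the median split: √0.637 = 0.798; 0.798 × 2.80 − 1.96 = 0.27; Φ(0.27) ≈ 0.61. For the flat score: 0.866 × 2.80 − 1.96 = 0.47; Φ(0.47) ≈ 0.68.

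**5. Checks.** With n = 510, a correlation of 0.124 is detectable with 80% power on the full scale. In 10,000 simulated data sets at that correlation, power was 80% with the full score and 60% after a median split. Recovering 80% after a median split would take 510 / 0.637 ≈ 801 patients. The power loss is nearly the same at N = 170, 255 and 340. Three groups compared without using their order do no better than a median split (about 60%). A 0–6 score cut in two loses about 35% if it is symmetric and bell-shaped, and about 23% if it is spread towards the extremes.

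**The case against.** **No cut is stated.** A reader might infer that the plan has decided to dichotomise age, literacy and locus of control, and so will lose a third or more of the information. The document does not support that. The sentence on SW weights names none of the three variables and could be served by stage, gender, education, line of treatment or country. The size of the loss depends on a grouping that nobody has written down. This objection stands, and it makes every figure above conditional.

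**The wording is open.** LCA is an alternative to subgroups in the DCE and can take continuous class-membership covariates. The closing paragraph, which does name the three variables, is a non-exhaustive list and is not confined to the DCE. This stands too. It limits the point to SW and the RPL-subgroup route, where no full-scale method is named.

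**The missing-data rule.** A reader might take it as proof that every patient will be placed in a subgroup on these scores. It is a conditional rule, in a sentence about unanswered demographic or treatment-history questions. It shows that subgroup assignment is envisaged and no more than that.

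**Coding of covariates belongs in the analysis plan.** Cut-points may well be set out there, and their absence here is not the point. The article names a type of method that needs grouping, and later cut-points would not restore the information lost by it.

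**A full model would be overloaded.** Six scores (age, two literacy measures and, as an assumption, three locus dimensions) times 7 to 10 attribute coefficients is 42 to 60 interaction terms, before any curvature. The 7 treats the three percentage attributes as linear (3 + 2 × 2); the 10 codes all five attributes by level (5 × 2). This objection is right and shapes the remedy.

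**Conclusion.** The point holds in conditional form. For a named clinical endpoint, subgroup comparison is the only SW-specific method given and one of two named DCE routes, although age, literacy and locus of control are graded. Analysing them on their full scale is a better choice and uses data already collected.

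The cost of grouping depends on how it is done. A two-group split of a roughly normal score with a linear gradient loses 36% at best and 51% at 20/80. A flat 0–6 score cut in two loses about 25%. Three to five ordered groups scored as a trend lose 10–21%. A loss of a third or more is therefore one scenario and not a property of the plan. Gender and stage group are unaffected. The LCA route is affected only if the scores are grouped before they enter it.

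**What to change.** In Statistical Analyses, state that wherever age, health literacy or locus-of-control scores are related to preference, they enter on their full scale:

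- **SW:** regress the attribute weights on the score instead of comparing subgroup means.
- **RPL:** use score-by-attribute interactions, one characteristic at a time or in a limited prespecified set, so that the model is not overloaded.
- **LCA, if used:** enter the scores as continuous class-membership covariates.
- **Linearity:** check it with a curvature term.
- **Subgroups:** keep subgroup results for these variables for display only. Gender, stage group, line of treatment and education stay as groups.

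The cost is some wording and extra modelling, with no new data or patients. The small downside is a linearity assumption, which the curvature term tests.
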